## Abstract

**Background:**

Delayed-onset post stroke cognitive impairment (PSCI) results from secondary neurodegeneration induced by stroke. Whereas targeted prevention or treatment strategies are still missing due to lack of evidences. This trial aims to evaluate the preventive effects of DL-3-n-butylphthalide (NBP) on delayed-onset PSCI.

**Methods:**

Effects of NBP on Delayed-onset Post Stroke Cognitive Impairment (End-PSCI) is a prospective, parallel-group, open-label, multicenter, randomized controlled trial with blinded outcome assessment. Hospital patients with acute cerebral infarction (within 2 weeks of onset) will be randomized into either standard medical therapy group or standard medical therapy combined NBP treatment group (NBP 200 mg, three times per day for 24 weeks). The primary outcome is the difference of incidence of delayed-onset PSCI between two groups. The secondary outcomes include difference of white matter degeneration, cognitive scores and prevalence of early-onset PSCI between two groups.

**Discussion:**

End-PSCI trial will provide evidences for NBP preventing delayed-onset PSCI. The secondary outcomes will also provide valuable insights into the pathogenesis of delayed-onset PSCI and mechanism of NBP’s actions.

**Trial registration:**

Trialsearch.who.int, ChiCTR2000032555, 2020/5/2, prospectively registered.

## Background

Post stroke cognitive impairment (PSCI) indicates cognitive impairment resulting from a stroke event, including post stroke dementia (PSD) and PSCI not fulfilling criteria for dementia [1]. Most PSCI occur in the early stage after stroke (early-onset PSCI), while some patients without early-onset PSCI will develop cognitive impairment months after stroke (delayed-onset PSCI) [2–5]. Data of the prevalence of delayed-onset PSCI (including PSD and PSCI not fulfilling criteria for dementia) is still in lack, while the prevalence of delayed-onset PSD varies largely from 4.4 to 23.9% according to a systematic review [6]. Though it seems lower comparing with early-onset PSD, the risk of dementia is still 1.6 to 10.3 times higher than that in stroke-free population. Study of these group of patients is important because there might be different mechanism from early-onset PSCI, which leads to a different optimal treatment plan.

Studies showed that early-onset PSCI mainly resulted from acute stroke lesions [7], while delayed-onset PSCI was found specifically associated with presence of severe cerebral small vessel diseases (CSVD) at baseline [6, 8]. Nevertheless, recent longitudinal studies have further indicated that the primary mechanism may be cerebral secondary degeneration (CSVD progression presented as increased white matter hyperintensity and cerebral atrophy) induced by acute stroke apart from baseline co-existent CSVD [9–11]. However, no interventional researches have been conducted to testify the role of secondary degeneration in its mechanism.

DL-3-n-butylphthalide (NBP) is a synthetic compound based on L-3-n-butylphthalide which is initially isolated from seeds of *Apium graveolens*. In 2005, the State Food and Drug Administration of China approved NBP as a therapeutic drug for ischemic stroke as it could significantly improve neurological function and exhibit good safety and tolerability, making it the first-class and recommended drugs in the Chinese guidelines of acute ischemic stroke. There is only one commercial dosage form of NBP in China: 100 mg for one soft capsule and 24 capsules in a bottle. Based on evidences of the multi-center phase 2 and 3 randomized controlled clinical trials [12, 13], oral administration of 200 mg NBP soft capsules, three times daily showed greatest effectiveness and good safety in the neurological recovery after acute ischemic stroke, thus has become the officially recommended dose. Massive evidences have found that NBP could achieve its protective function through multitargeted actions: antiplatelet aggregation and antithrombotic effects, protection of mitochondria, anti-oxidant, anti-apoptosis, improvement of cerebral microcirculation, promotion of neurogenesis and poststroke brain tissue recovery, etc. [14] Clinical researches have also testified that combined treatment of NBP might improve cerebral hypoperfusion in the patients with carotid artery atherosclerotic stenosis [15] and may improve revascularization and inhibit inflammation in acute stroke patients (reflected by blood biomarkers) [16–18]. What’s more, recently, both animal and clinical researches have validated that NBP could alleviate ischemia-induced cognitive deficits and one target could be white matter degeneration [19–22]. Hence, based on possible mechanisms of delayed-onset PSCI and NBP’s action targets, we hypothesized that NBP may have preventive efficacy for delayed-onset PSCI (including PSD and PSCI not fulfilling criteria for dementia) and then designed the present study.

## Methods

### Design

Effects of NBP on Delayed-onset Post Stroke Cognitive Impairment (End-PSCI) is a prospective, parallel-group, open-label, multicenter, randomized controlled trial with blinded outcome assessment. Hospital patients within 2 weeks of cerebral infarction onset will be randomized into either standard medical therapy group or standard medical therapy combined NBP treatment group. A set of validated cognitive tests and blood samples collection will be implemented at acute phase (within 2 weeks of onset), 6 weeks, 12 weeks and 24 weeks after stroke. Brain magnetic resonance imaging (MRI) including T1, T2 and T2 Fluid-attenuated inversion recovery imaging (most are clinical routine scans with some high resolution, isotropic scans) will also be performed at acute phase and 24 weeks after stroke. An independent Data and Safety Monitoring Board (DSMB) will regularly monitor safety during the study. The trial has been approved by the Institutional Review Board/Ethics Committee in the First Affiliated Hospital of Xi’an Jiaotong University (approval number: XJTU1AF 2020LSK-032). Figure 1 this study is ongoing (recruitment not completed) at the time of submission.

**Fig. 1 Fig1:**
[figure not shown]
Flow chart of End-PSCI trial. This is the flow chart of End-PSCI trial. Hospital patients with acute cerebral infarction (within 2 weeks of onset and with MRI evidences) will be randomized into either standard medical therapy group or standard medical therapy combined NBP treatment group. Cognitive function will be tested during the 24-week follow-up. MRI: magnetic resonance imaging, NBP: DL-3-n-butylphthalide

### Patient population

Hospital acute cerebral infarction patients confirmed by MRI will be enrolled and randomized within 2 weeks of onset. The detailed inclusion and exclusion criteria are listed in Table 1.

**Table 1 Tab1:** Inclusion and exclusion criteria of End-PSCI

**Inclusion criteria**	
1. Age ranges from 50 to 75 years (50 and 75 also included), no gender limitation.	
2. Meet the diagnostic criteria of Chinese guidelines for diagnosis and treatment of acute ischemic stroke 2018^a^ [23].	
3. Brain MRI provides evidences for the diagnosis of acute cerebral infarction.	
4. No disturbance of consciousness, evident aphasia or severe paralysis.	
5. Educational level should be primary school or above, with capability of finishing cognitive tests.	
6. Signed written informed consent.	
**Exclusion criteria**	
1. Patients treated by intravenous or arterial thrombolysis or endovascular interventional therapy.	
2. Patients with secondary hemorrhage or hematoma after cerebral infarction.	
3. Patients with pre-stroke cognitive impairment.	
4. Patients with other severe central nervous systematic diseases: Alzheimer’s disease, Parkinson’s disease, dementia with Lewy bodies, frontotemporal dementia, neuromyelitis optica, epilepsy, central nervous system infection, cerebral injury, cerebral tumor, etc.	
5. Patients with mental disorders diagnosed by the Diagnostic and Statistical Manual of Mental Disorders—Fourth Edition Text Revision (DSM-IV-TR) [24], including schizophrenia, bipolar affective disorder, major depressive disorder or delirium, etc.	
6. Patients are taking cholinesterase inhibitors, Memantine or NBP.	
7. Patients with uncorrectable visual or hearing disturbances severe enough to preclude cognitive tests.	
8. Patients with unstable or severe cardiovascular, respiratory, gastrointestinal, hepatic, renal or hematopoietic system disease.	
9. Unable to perform MRI tests.	
10. Patients who are unwilling or unable to comply with the protocol or cannot/will not cooperate fully with the investigator.	

^a^The following should all be met: 1) Acute onset; 2) With focal neurological function defects (e.g. one side limb weakness, numbness of one side of the face or language disorders), a few with general neurological function defects; 3) Responsible lesions on imaging or symptoms/signs lasted more than 24 h; 4) Excluded non-vascular etiology; 5) Brain CT/MRI excluded cerebral hemorrhage

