**Fig. 2 Fig2:**
[figure not shown]
Schedule of End-PSCI. This is the schedule of End-PSCI trial. After enrolment and allocation, general information will be recorded at baseline. The treatment of standard medical therapy and standard medical therapy combined NBP treatment will last for 24 weeks after stroke. For every follow-up visit (baseline, 6 weeks, 12 weeks and 24 weeks after stroke), vital signs and medical history, application of study drugs, application of combined drugs, NHISS and MRS scores, a set of validated cognitive tests, blood samples collection and adverse events record will be implemented. Carotid Doppler ultrasonography and brain MRI including T1, T2 and T2 Fluid-attenuated inversion recovery imaging will also be performed at baseline and 24 weeks after stroke. NHISS: National Institutes of Health Stroke Scale; MRS: Modified Rankin Scale; MRI: Magnetic Resonance Imaging; FLAIR: axial fluid-attenuated inversion recovery

Notably, long-term use of two types of drugs should be avoided in all enrolled patients. One is that may influence cerebral microcirculation or metabolism such as Nimodipine, Idebenone, Oxiracetam and some traditional Chinese medicine that have blood activating and stasis removing effects. Another type is that may influence cognitive function such as cholinesterase inhibitors, Memantine and antipsychotic drugs. If happens, this will be treated as drop-out.

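### Five of the seven drugs or classes whose long-term use counts as drop-out are not named at entry, so some current users can be randomised and then lost

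*Protocol article*

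**What the plan says.** Table 1, exclusion criterion 6, bars current users of three things: "Patients are taking cholinesterase inhibitors, Memantine or NBP".

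The Interventions section, in the text after Fig. 2, sets the on-study rule: "Notably, long-term use of two types of drugs should be avoided in all enrolled patients". The first type acts on cerebral microcirculation or metabolism, "such as Nimodipine, Idebenone, Oxiracetam and some traditional Chinese medicine that have blood activating and stasis removing effects". The second acts on cognition, "such as cholinesterase inhibitors, Memantine and antipsychotic drugs". The consequence follows: "If happens, this will be treated as drop-out".

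Two other criteria in Table 1 bear on the matter. Criterion 5 excludes DSM-IV-TR mental disorders, "including schizophrenia, bipolar affective disorder, major depressive disorder or delirium, etc". Criterion 10 excludes "Patients who are unwilling or unable to comply with the protocol or cannot/will not cooperate fully with the investigator".

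The Discussion gives the reasons for the restriction. Drugs of the first type may share targets with NBP and are not part of routine guideline treatment of cerebral infarction. Drugs of the second type may affect the cognitive outcomes and are recommended only in confirmed dementia or mental illness.

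**The concern.** A drug whose continued use ends a patient's participation would normally be checked before randomisation, when declining to enrol costs nothing in validity. Here the entry list is shorter than the on-study list. The thresholds also differ: criterion 6 applies to anyone taking a drug, whereas the on-study rule applies to long-term use, which the article does not define.

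A patient already on one of the unnamed drugs may therefore be randomised and later become a post-randomisation loss that screening could have avoided. Three features of the plan make such losses matter:

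- **Known allocation.** The trial is open-label, and under Study organization the principal investigators, usually the attending doctors, handle enrolment, allocation and follow-up. Whether a pre-existing medicine goes on is settled with the arm known, so the resulting drop-outs could differ by arm.
- **Analysis population.** The main population under Statistical analyses needs at least one follow-up assessment, and the first is at 6 weeks. A patient lost before then is not analysed.
- **Outcome window.** The primary outcome is impairment that develops 3 to 6 months after stroke. If cognitive testing ends at drop-out before month 3, carrying scores forward cannot show onset in that window.

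**Working it through.** **Step 1. Compare the two lists.** Inputs are criterion 6 (Table 1) and the on-study list (Interventions).

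| Named in the on-study rule | Named in criterion 6 | Other criterion that may apply |
|---|---|---|
| Cholinesterase inhibitors | Yes | - |
| Memantine | Yes | - |
| Antipsychotics | No | 5 (by diagnosis), 10 |
| Nimodipine | No | 10 |
| Idebenone | No | 10 |
| Oxiracetam | No | 10 |
| Blood-activating traditional medicines | No | 10 |

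Named on study: 7. Also named in criterion 6: 2. Not named: 7 − 2 = 5. Both on-study types are given by example, so seven is a minimum. NBP, the third entry in criterion 6, is the study drug. Neither the criteria nor the Interventions text gives a washout.

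**Step 2. Follow a current user through the rules.**

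1. The patient takes one of the five and has no diagnosis under criterion 5.
2. If recognised at screening as unwilling or unable to stop, the patient is excludable under criterion 10.
3. If the patient stops at enrolment, there is no long-term use on study and the drop-out rule is not met.
4. If the patient is not recognised at screening, or means to stop but continues or resumes long term, the patient has been randomised and is counted as a drop-out.

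Only route 4 produces the loss. The article gives no figure for how many patients would take it.

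**Step 3. Reproduce the sample size for context.** Inputs from Sample size: 4.4% against 2.2% (a 50% reduction), 1200 per group, 20% drop-out, 3000 in total. Two-sided 5% comes from Statistical analyses. Power is not stated.

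- Total: 2 × 1200 / (1 − 0.20) = 3000, as stated.
- Per group: n = [z₀.₉₇₅ √(2p̄q̄) + z_power √(p₁q₁ + p₂q₂)]² / (p₁ − p₂)², with p̄ = 0.033. This gives 1034 at 80% power, 1183 at 85% and 1384 at 90%. The stated 1200 fits an assumed 85%; power at 1200 per group is 85.5%.
- Expected events: 0.044 × 1200 ≈ 53 and 0.022 × 1200 ≈ 26.

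**Step 4. Illustration by assumption only.** Suppose 2%, 5% or 10% of 3000 patients took route 4, equally in both arms and all in addition to the planned 20%. The drop-out allowance is 0.20 × 3000 = 600.

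| Assumed share | Patients | As share of 600 | Left per arm, 1500 × (1 − 0.20 − share) | Power |
|---|---|---|---|---|
| 0% | 0 | 0% | 1200 | 85.5% |
| 2% | 60 | 10% | 1170 | 84.6% |
| 5% | 150 | 25% | 1125 | 83.2% |
| 10% | 300 | 50% | 1050 | 80.6% |

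The shares have no source in the article. The table shows only that balanced losses of this size would cost little power. With about 53 and 26 expected events, imbalance between arms is the more serious possibility, and nothing in the article allows it to be sized.

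**The case against.** Much of the opposing case stands.

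- **Lists may differ.** Current use of a cholinesterase inhibitor or memantine points to a condition that criteria 3 and 4 already exclude, and earlier NBP would contaminate the comparison. Barring some drugs at entry and restricting others on study is not in itself a contradiction.
- **A reader might infer that every such user meets the drop-out rule from day one.** The text does not support this. The rule concerns long-term use in enrolled patients and operates only if such use occurs, so a patient who stops at enrolment does not breach it.
- **A reader might infer that nothing in Table 1 reaches these patients.** Criterion 5 removes many antipsychotic users, and criterion 10 can remove a patient known to be unwilling or unable to comply. Criterion 10 is general, however, and depends on the site asking about drugs that criterion 6 does not mention. It does not catch a patient who agrees to stop and then continues.
- **A reader might infer that most of these losses fall before the first follow-up visit and so outside the main population.** The article does not say so. Per the Fig. 2 legend, combined drugs are recorded at the same visits as cognitive testing, so use found at 6 weeks may come with the one follow-up assessment required.
- **Numbers may be small.** The Discussion describes first-type drugs as outside routine guideline treatment, so use at entry could be low.
- **Drugs started after randomisation** raise the same arm-related problem, and an entry criterion cannot prevent that.

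What the objection does not remove is that five named drugs or classes trigger drop-out on study without being named at entry. Table 1 is presented as the detailed list of criteria, so the gap is not merely one of condensation.

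**Conclusion.** The point holds in a limited form. Two of the seven drugs or classes in the on-study rule are named in criterion 6 and five are not. A current user of one of the five who is caught by neither criterion 5 nor criterion 10 can be randomised and, if use continues long term, becomes an avoidable post-randomisation loss. With allocation known to the treating investigators, such losses could differ by arm; that they would is not shown.

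The number of patients affected cannot be derived from the document, and the ranges shown rest on assumed shares. Nothing here contradicts the stated 1200 per group or 3000 in total. This is a clear and cheaply repaired inconsistency, not a flaw that undermines the trial.

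**What to change.** 1. Reconcile criterion 6 in Table 1 with the on-study rule in Interventions, so that entry and follow-up refer to one list with one meaning of long-term. Which drugs belong on it, and how current use at screening is to be handled, are clinical decisions for the sponsor.
2. Check that list before randomisation. The Fig. 2 legend already has combined drugs recorded at baseline, so no new data item is needed. The legend describes the recording of general information at baseline as following enrolment and allocation, so the amendment should state that the drug check comes first.
3. Keep any patient randomised while on a listed drug in outcome follow-up and in the main analysis as randomised, with baseline use flagged. This concerns outcome data only and implies nothing about treatment.

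The Design section says recruitment was not complete at submission, so an amendment could still help patients not yet enrolled. The cost is one reworded criterion and slightly more screen failures. It will not prevent losses from listed drugs started after randomisation.

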### Randomization

Eligible patients will be randomly allocated to receive either standard medical therapy or standard medical therapy plus NBP treatment (1:1) using block randomization in blocks of eight. The randomization code list will be generated by an independent statistician and directly allocated to the main investigators in every center so that the independent and specialized cognitive evaluators and the diagnostic group will be blinded.

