### Statistical analyses

A customized online database will be used to manage data and SPSS version 25.0 will be used for all analyses. Group t-test, Mann-Whitney u test or χ2 test will be conducted for comparisons between two groups according to different types of variables. Occurrence of delayed-onset and early-onset PSCI will be analyzed as categorical data (yes or no). χ2 test will be used to compare the incidence between two groups and multivariate logistic regression will be used to adjust confounders. Paired sample t-tests or Wilcoxon matched-pairs signed-ranks test will be used to compare WMH degree (visual scale scores and WMH volume) and total cognitive scores at different time point within each group. Changes of WMH degree (indicating degeneration) and total cognitive scores from baseline to 24 weeks will be compared between two groups using Group t-test or Mann-Whitney u test and multivariate linear regression will be used to explore the contributing factors. Changes of cognitive scores will further be dichotomized as improved and unimproved group to do the analysis, improvement is defined as score change < 0 for Alzheimer’s Disease Assessment Scale-Cognitive subscale or > 0 for Montreal cognitive assessment scale. Furthermore, Kaplan–Meier analysis and cox proportional hazards analysis will also be performed to compare the incident rate of any cognitive impairment between two groups and explore contributing factors. Two-sided value of *p* < 0.05 will be considered significant.

Outcomes will be measured both for intention-to-treat population (main analysis population) and the per protocol population. The intention-to-treat population consist of those who have a complete baseline assessment as well as at least one follow-up assessment for the primary outcome variables. Missing values of cognitive scores will be replaced by last observation carried forward method. The per protocol population consist of those who complete the 24-week follow-up with no major protocol violations.

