### Study organization

The study organization includes: (1) Steering Committee; (2) DSMB; (3) Executive Committee. The Executive Committee includes principal investigators (usually the attending doctors) in every center, independent and specialized cognitive evaluators in every center and senior neurologists from the main center who will make the final diagnosis. The principal investigators are responsible for enrolment, allocation and follow-up visit. The evaluators will perform cognitive testing in a separate examination room without knowing the patients’ any information except name and educational level. The diagnostic group will make the final diagnosis based on clinical information (not including allocation and medication administration record). All investigators will undergo standard training courses on study protocol and confidentiality. The independent cognitive evaluators will also be trained not to ask or answer any questions about the patients’ information and be assessed for consistency before getting certification for cognitive tests.

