Notably, two types of treatment should be avoided in our study as the first type may act on some same targets with NBP and the second type may influence the cognitive outcomes. The avoidance of first type of treatments will not interfere with the optimal treatments because these are not recommended in routine treatment of cerebral infarction according to the Chinese official guidelines. The second type of treatments are only evidentially recommended in patients with confirmed diagnosis of dementia or mental illness. For patients with confirmed or suspicious diagnosis of newly dementia or mental illness, treatment plan will be determined by doctors and negotiated with patients or caregivers according to patients’ condition. If these treatments are applied, patients will be treated as drop-out, or on the contrary, continue in the study. Confirmed early-onset PSCI patients will continue in the study unless they take medications that should be avoided during the study, which will be recorded and treated as drop-out. With proper informed consent, the treatment plan will be negotiated with these patients or caregivers to decide whether they will continue in the study. These patients will be given routine treatments immediately after the last visit if necessary. Notably, the confirmation of early-onset PSCI will be made at least 3 months after the symptom, and the visit plan is at about 1, 3 and 6 months, which will not significantly delay the treatment.

One drawback of End-PSCI trial is the open-label nature. The main aim of the present study is to investigate the preventive effects of NBP on delayed-onset PSCI, and the primary outcome is defined as the difference of incidence of delayed-onset PSCI between study group and control group. However, due to the lower incidence of delayed-onset PSCI, the sample size would be about 3000 patients with acute cerebral infarction from the calculation based on the primary outcome, therefore will cost too much to provide placebo medicines. Hence, we design this study as open label. To avoid bias, efforts have been made by blinded outcome assessment that allocation will be blinded from all cognitive evaluators and senior neurologists who make the final diagnosis.

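### As written, allocation is not concealed: the code list goes to centre investigators, who also enrol and allocate in an open-label trial

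*Protocol article*

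**What the plan says.** The Randomization section of the protocol article allocates patients 1:1 "using block randomization in blocks of eight". On handling of the list it states: "The randomization code list will be generated by an independent statistician and directly allocated to the main investigators in every center". The purpose follows in the same sentence: "so that the independent and specialized cognitive evaluators and the diagnostic group will be blinded".

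The Study organization section describes "principal investigators (usually the attending doctors) in every center" and adds: "The principal investigators are responsible for enrolment, allocation and follow-up visit".

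Treatment is not masked. The Discussion explains that placebo for about 3000 patients would cost too much and concludes: "Hence, we design this study as open label". The remedy it offers for bias is blinding of the cognitive evaluators and of the neurologists who make the final diagnosis. The Design section says that recruitment was not complete at submission.

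**The concern.** Independent generation of the list protects the sequence only until someone who recruits can read it. Here the list goes to the centres, and the centre investigators decide who enters and carry out the allocation.

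Several entry criteria in Table 1 need judgement: whether paralysis is severe, whether the patient can complete cognitive testing, and whether the patient will comply and cooperate. The two-week entry window also leaves some freedom over timing. An investigator who knows the next arm could, without any deliberate intent, apply these criteria differently to a frail and a fit patient.

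Blinded outcome assessment deals with how events are judged. It does nothing about who entered each arm. If the arms differ in prognosis from the start, the comparison of delayed-onset PSCI is biased, and the planned logistic regression can correct only for factors that were measured. Events are expected to be few, so a modest prognostic imbalance can matter.

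**Working it through.** **1. The plan's own figures.** The Randomization section contains no calculation. The Sample size section gives 1200 per group and 20% drop-out: 2400 / (1 − 0.20) = 3000, which agrees. With 4.4% v 2.2% and two-sided alpha 0.05, the usual two-proportion formula gives 1183 per group at 85% power, close to 1200. The article states no power. None of this affects the present point. It supplies the rates and group sizes used below.

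**2. The passages side by side.**

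| Question | Answer in the article | Section |
|---|---|---|
| Who generates the list? | An independent statistician | Randomization |
| Who receives it? | Main investigators, every centre | Randomization |
| Who enrols and allocates? | Principal investigators, every centre | Study organization |
| Who is blinded? | Cognitive evaluators, diagnostic group | Randomization, Study organization, Discussion |
| What withholds the next assignment from the recruiter? | Nothing stated | – |

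With an open list in hand, 100% of upcoming assignments are known.

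**3. Predictability without the list.** Assume that blocks of eight run within centre, that the recruiter knows the block size (it is published), and that the recruiter tracks past open-label assignments. Write the block as 2b with b = 4; there are C(8,4) = 70 equally likely orders.

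- Expected number certain in advance: 2b/(b + 1) = 8/5 = 1.6 of 8, or 20%.
- Expected correct guesses, always guessing the arm with more places left: b + 2^(2b−1)/C(2b,b) − 1/2 = 4 + 128/70 − 0.5 = 5.33 of 8, or 66.6%, against 50% under simple randomisation.

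Enumerating all 70 orders gives the same two results.

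**4. Illustration of what steering could do.** Every input in this step except the 4.4% and the group sizes is an assumption. Suppose 20% of patients carry 11% risk and 80% carry 2.75%: 0.20 × 0.11 + 0.80 × 0.0275 = 0.044. The drug has no effect. Expected events at 1200 per arm are 2400 × 0.044 = 105.6, about 106. (The planned-effect total, 1200 × 0.044 + 1200 × 0.022 = 79, belongs to a different scenario.)

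If 15% of the NBP arm and 25% of the control arm are high-risk:

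- NBP: 0.15 × 0.11 + 0.85 × 0.0275 = 3.99%
- Control: 0.25 × 0.11 + 0.75 × 0.0275 = 4.81%; risk ratio 0.83
- Standard error under the pooled rate: √(2 × 0.044 × 0.956 / 1200) = 0.00837; the unpooled value is the same to this precision
- Chance of a significant apparent NBP benefit: Φ((0.00825 − 1.96 × 0.00837) / 0.00837) = Φ(−0.975) = 16.5%

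The same formula over a range, with no covariate adjustment:

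| High-risk share, NBP v control | Risk, high v low | Risk ratio | False benefit, 1200 per arm | 1500 per arm |
|---|---|---|---|---|
| 20% v 20% | 11% v 2.75% | 1.00 | 2.5% | 2.5% |
| 19% v 21% | 11% v 2.75% | 0.96 | 3.9% | 4.1% |
| 18% v 22% | 11% v 2.75% | 0.93 | 5.9% | 6.4% |
| 15% v 25% | 6.6% v 3.85% | 0.94 | 5.1% | 5.6% |
| 15% v 25% | 8.8% v 3.3% | 0.88 | 9.6% | 11.0% |
| 15% v 25% | 11% v 2.75% | 0.83 | 16.5% | 19.5% |

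The last row implies 180 v 300 high-risk patients per 1200, a baseline difference of z = 0.10 / √(2 × 0.2 × 0.8 / 1200) = 6.1. For a measured factor that would be plain in the baseline table. The smaller split of 18% v 22% gives z = 2.4.

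**The case against.** The strongest reply is that one sentence in a condensed article does not settle how the codes travel. It does not say whether they arrive as an open list, sealed, or one at a time, and such detail often sits in a full protocol, which is not shown. The article also writes main investigators in one section and principal investigators in the other. Both caveats stand, and they are why the point is worded as what the text describes. They do not remove it. The article states a positive procedure in which the list goes to the centres, describes no separate role for its recipients, and gives assessor blinding as the reason.

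The block size is rightly called secondary. If recruiters hold the list it adds nothing, and the 20% and 66.6% figures need blocking within centre, which the text implies but does not state.

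The illustration is fairly criticised too. Its risk strata and steering shares come from no source, and the larger splits would be visible, and largely adjustable, if the factor were measured. It shows a mechanism and estimates nothing.

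A reader might infer that enrolment has in fact been steered, or that this is the likeliest way for the trial to reach a false positive. The article supports neither. It reports no enrolment data, and it contains at least one other route: the primary diagnosis relies in part on concerns voiced by patients, informants or clinicians, and patients know their treatment.

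**Conclusion.** The point holds as a defect in the stated procedure: on the article's own words, allocation is not concealed from those who enrol, and the safeguards described address a different bias. It should be put right while patients are still being recruited, because analysis cannot reliably repair selective entry afterwards.

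In terms of knowledge, the exposure is all upcoming assignments for a recruiter with an open list, or 20% certain and 66.6% guessable for one with only the block size and past assignments. How much bias follows cannot be derived from the documents. Under the assumptions tried, the unadjusted chance of a false benefit runs from barely above 2.5% to about 16% at 1200 per arm. The conclusion rests on reading main and principal investigators as the same people and on no unstated concealment step. The block figures also rest on blocking within centre.

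**What to change.** - Keep the list with the independent statistician or in a central system. Release each assignment singly, only after eligibility, consent and baseline cognitive scores are recorded.
- For the remaining patients, replace the fixed block of eight with randomly varying block sizes that are not disclosed to the centres.
- For patients already randomised, compare baseline characteristics by arm before and after the change. Adjust the primary analysis for prognostic baseline factors specified in advance. I would not split the primary result by these two periods: about 79 events are expected under the planned effect, and dividing them would tell little.
- If a concealed release procedure is already in use, leave it in place and correct the Randomization and Study organization sections to describe it.

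The cost is a short amendment and a randomisation module or equivalent central release. The article says of its existing system only that "A customized online database will be used to manage data", so whether it can host such a module needs checking. The sample size does not change.
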